### Data collection

Data collection will be conducted by the study researchers via telephone, email or online at baseline (before medication commencement) and at weeks 4, 8, 10, 14 and 18. Week 10 data collection will act as the cross-over secondary baseline for analysis purposes. Data will be entered into CRFs by dedicated trained staff. Each participant will receive up to seven face-to-face or telephone consultations with the trial pharmacist to commence treatment, monitor progress and adjust the dose of the study medication over the 8-week treatment periods. These visits will also incorporate a medical evaluation and collection of primary and secondary outcomes. Participants will receive usual neurosurgical care independent of and parallel to PAGPROS.

The use of prior and continued analgesic medicines will be collected at baseline. Adherence to study medication will be documented through a self-reported daily medication diary and by counting the returned medicine compared with the prescribed regimen as recorded by the trial pharmacist. Participants will be asked to return used and unused study medications at each visit.

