### Randomisation and blinding

The trial pharmacist (un-blinded) will generate a randomisation code using a computer-derived permuted block with varying block size sequence. Manufacturing and preparation of the medication capsules will be performed by an external good manufacturing practice-accredited facility. The unblinded pharmacist will be involved in the preparation of the medication kits as per the randomisation schedule. The sequence will follow a 2 × 2 sequential design whereby participants will receive PGB first, then GBP (or vice versa), in a double-blinded fashion. Owing to the variability in regular dosage frequency between the medications (PGB twice daily, GBP thrice daily), study medication packs will contain three bottles each, correlating to the dosage times of morning, lunchtime and night, so as to maintain blinding. Medication packs pertaining to the PGB arm will have placebo incorporated as the lunchtime dose with all medications being indistinguishable. The randomisation schedule will remain concealed from other researchers. Placebo capsules will have an appearance identical to the active capsules. The randomisation process will ensure concealed allocation and blinding of the specialist, the participant and the outcome assessor.

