### Study treatment

Participants will be randomised to commence treatment on either PGB or GBP. As a result of the cross-over methodology, participants will have the opportunity to experience both PGB and GBP, and we predict little or no carry-over effects (medium- or long-term) after the washout period. We believe the incorporation of a stand-alone placebo arm is unethical in trials where participants with moderate to severe pain are recruited.

The starting dose of PGB is 150 mg once daily for the first week. This will be titrated to the participant’s optimal dose up to a maximum of 300 mg twice daily, depending on their progress and tolerance at each dose level. The starting dose for GBP is 400 mg once daily for the first week. This will be titrated to the participant’s optimal dose up to a maximum of 800 mg thrice daily, depending on their progress and tolerance at each dose level. These doses are based on national recommendations from the Australian Medicines Handbook [11]. In the standard study dosing regimen (Table 1), we expect a 4-week titration period, after which the maximum tolerated dose for each participant will be maintained for 4 weeks before the first study medication is ceased in preparing for washout. The washout period between treatment phases will last 1 week, which is sufficient for these medications because they possess a short half-life (5–7 h). The dosage of either PGB or GBP can be amended at any stage in PAGPROS on the basis of efficacy and/or SEs by communication between the study specialist and the study pharmacist. The maximum treatment period is 8 weeks [13].

**Table 1 Tab1:** PAGPROS medication titration schedule

	Medication	Total daily dose
Week	Pregabalin	
1	1 × 150-mg capsule in the morning	150 mg/day
2	1 × 150-mg capsule three times daily (middle dose is placebo)	300 mg /day
3–8	2 × 150-mg capsules three times per day (middle dose is placebo)	600 mg/day
Week	Gabapentin	
1	1 × 400-mg capsule in the morning	400 mg/day
2	1 × 400-mg capsule three times per day	1200 mg/day
3–8	2 × 400-mg capsules three times per day	2400 mg/day

*PAGPROS* Pregabalin and Gabapentin Prospective Clinical Trial for the Treatment of Sciatica: A Randomised, Double-Blind, Cross-over Study

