### Sample size

We hypothesise that over an 8-week treatment period, GBP will reduce pain on the VAS scale by an average of 4.5 points from (7.5 to 3.0) as per historical literature [16]. We predict PGB to show at least the same benefit. We hypothesise that PGB will display superiority over GBP by at least a 20% better relative reduction in VAS score, with a resultant reduction of 5.4 (from 7.5 to 2.1) points from baseline. This 20% relative reduction is based on the average reduction of pain symptoms compared with placebo for indirect comparisons [1, 16]. Relative reduction will be used because it is often more impressive and also to allow for the instance of a lower-than-expected event rate, which would lower the absolute risk reduction.

If the true difference in means of both arms of the study is 0.9 with an SD of 1.2, in order to detect this 20% relative decrease in pain between GBP and PGB, we will need to study 30 patients (15 per treatment arm) to reject the null hypothesis with 80% power. The type I error probability associated with this test of the null is 0.05. Assuming a 20% drop-out rate, the total sample size will be 38 patients (19 per treatment arm). We have chosen this large effect size and conservative SD on the basis of anecdotal and specialists’ experience with this cohort of patients. The benefits of the cross-over methodology are evident with the small sample size required, owing to each participant acting as his/her own control. If this were a conventional parallel study design, the sample size needed would be approximately 100 participants. We conservatively estimate that if two people can be recruited per week, the study duration will be approximately 1.5 years.

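### Dose decisions are not kept blind: the un-blinded trial pharmacist conducts the dose-adjustment visits and is party to every amendment, so the dose reached can depend on knowledge of the drug

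*Protocol article*

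**What the plan says.** Four parts of the protocol article bear on this.

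- **Randomisation and blinding.** "The trial pharmacist (un-blinded) will generate a randomisation code using a computer-derived permuted block with varying block size sequence". It continues: "The unblinded pharmacist will be involved in the preparation of the medication kits as per the randomisation schedule". The section names the specialist, the participant and the outcome assessor as blinded. The pharmacist is not on that list, and Participants and recruitment also calls the pharmacist unblinded.
- **Data collection.** Each participant has up to seven consultations with the trial pharmacist, held to start treatment, follow progress and "adjust the dose of the study medication over the 8-week treatment periods".
- **Study treatment.** Each drug is taken to an individual optimum below a cap, guided by progress and tolerance. The dose may also be changed at any stage "on the basis of efficacy and/or SEs by communication between the study specialist and the study pharmacist".
- **Study treatment, Table 1.** This gives a default schedule by week. The number of capsules at each step is the same for both drugs.

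**The concern.** Double-dummy packaging hides the drug from the patient. It does not hide it from the person at the visit where progress is judged and the dose is changed. If that person knows the drug, one drug may be taken further, or reduced sooner, than the same clinical picture would have led to under blinding. No intent is needed: knowing which drug a complaint of dizziness belongs to could be enough.

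Both co-primary outcomes (leg-pain VAS and ODI) and the key secondary outcome (side effects) can respond to dose. A dose difference created by knowledge of the allocation would then be read as a difference between the drugs. The cross-over gives no protection, because each patient meets the same arrangement in both periods and the distortion follows the drug.

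**Working it through.** **1. Who is blind and who touches the dose**

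| Role | Blinding status | Part in dosing |
|---|---|---|
| Trial pharmacist | Un-blinded; generates the code and helps prepare the kits | Holds the visits at which progress is followed and the dose adjusted; party to amendments |
| Study specialist | Stated to be blinded | Party to amendments |
| Participant, outcome assessor | Stated to be blinded | No dosing role stated |

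Study treatment speaks of the study pharmacist and Data collection of the trial pharmacist. The article describes only one pharmacist role, so I take them to be the same.

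**2. Is there discretion to influence?** Table 1 is a default. Study treatment allows departures at any time on efficacy or side effects, and the weaknesses section on treatment duration says each participant stays on their own maximum tolerated dose. The dose reached is therefore partly a matter of judgement.

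**3. Does the cross-over cancel the effect?** Let tP and tG be the true mean effects of pregabalin and gabapentin. Let bP and bG be the mean outcome shifts that arise because the dose reached differs from the one a blinded decision would have given. In the within-patient contrast the patient effect drops out, and the period effect balances over the two sequences. What remains is

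expected contrast = (tP - tG) + (bP - bG).

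The second bracket is zero only if knowledge of the drug shifts both drugs equally. Nothing in the design ensures that.

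**4. Reproducing the plan's own figure.** Inputs from Sample size: difference 0.9, SD 1.2, type I error 0.05 (two-sided assumed), power 80%. Reading 1.2 as the within-patient SD:

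- standard error at N = 30: 1.2 x sqrt(2/30) = 0.310
- noncentrality: 0.9 / 0.310 = 2.90, with 28 degrees of freedom
- power: 80.1%, so N = 30 is reproduced
- drop-out: 30 / 0.80 = 37.5, rounded up to 38, as stated.

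The sample size is not in dispute here. It supplies the setting for the next step.

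**5. Scale, by assumption only.** Suppose there is no true difference and bP - bG takes the value shown. The two-sided 5% test with 30 patients would then reject this often:

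| Assumed shift (VAS points) | 1.2 = within-patient SD | 1.2 = SD of the paired difference |
|---|---|---|
| 0.1 | 6% | 7% |
| 0.2 | 10% | 14% |
| 0.3 | 15% | 26% |
| 0.45 | 29% | 51% |

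The documents give none of these shifts. The table shows how sensitive the test is to a shift, not how large the shift would be.

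**The case against.** The strongest reply is that the documents do not say the pharmacist decides. Amendments are made "by communication between the study specialist and the study pharmacist", and the specialist is listed as blinded. The specialist may decide and the pharmacist merely carry it out. This stands in part: a reader might infer that the un-blinded pharmacist runs titration alone, and the text does not support that. The narrower point survives, because the pharmacist conducts the adjustment visits, is party to each amendment, and nothing stated keeps knowledge of the drug out of the decision.

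Other stronger readings also fail:

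- **The specialist is unblinded by these exchanges.** This is conjecture. Nothing says they are conducted in milligrams or by drug name, and matching capsule counts make a masked exchange possible.
- **The pharmacist will favour pregabalin.** Sample size does state: "We hypothesise that PGB will display superiority over GBP by at least a 20% better relative reduction in VAS score". But the primary objective is open in both directions, the Background argues that neither drug should be favoured, and no expectation is attributed to the pharmacist, who is described as independent of the treating team.
- **The bias can be put at half the target difference.** If benefit were proportional to dose and 20% of gabapentin periods were held at 1200 instead of 2400 mg/day, the loss would be 0.20 x 0.5 x 4.5 = 0.45 points against a target of 0.9. Both premises are invented. The 4.5-point fall is a change from baseline, which need not halve when the dose halves. Nor is every step two-fold: gabapentin's first step in Table 1 is 400 to 1200 mg/day, three-fold.
- **The problem would be invisible.** It would not be entirely so. The prescribed regimen, diaries and returned-medicine counts allow the dose reached to be compared by drug. Such a comparison would show an imbalance but could not separate bias from a true difference in tolerability.

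It is also fair that Table 1 sets a common default and a cap for each drug, which limits the discretion. Finally, the full protocol may give details of masking. The article, however, positively assigns dose adjustment to visits with the un-blinded pharmacist, so this is a stated arrangement and not a detail left out.

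**Conclusion.** The point holds in a limited form. As written, the blinding, treatment and data-collection sections do not keep dose decisions blind, and this opens a route to a drug-linked bias that the within-patient contrast passes on in full. It is an open route, not a demonstrated bias. Its size and direction cannot be derived from the documents, and the rejection rates above depend on assumed shifts, a two-sided test and the reading of the SD. The conclusion rests on two readings of the text: that the study pharmacist and the trial pharmacist are the same role, and that the permitted departures from Table 1 are used in practice.

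**What to change.** Reconcile Randomisation and blinding, Study treatment and Data collection so that:

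- the blinded study specialist, or another blinded member already in the team, makes each dose decision within the existing schedule;
- the reports of progress and side effects behind the decision reach that person without passing through the pharmacist;
- requests are expressed in Table 1 capsule counts, never in milligrams or drug names;
- the un-blinded pharmacist only dispenses what is requested;
- the dose level reached is tabulated by drug and period for all participants, including those already completed.

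This changes who decides and how the request is masked. It proposes no change to any dose or titration rule.

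**Cost.** No new staff and a short request form, but the specialist takes on more dose queries. Under Modification of the protocol, a formal amendment with ethics approval is needed. Trial status reports 18 participants completed, so of the planned 38 at most 38 - 18 = 20 could benefit, fewer if some are part-way through. The trial would then contain two decision procedures, so the date of the change should be recorded and reported. For those already treated, the dose table is the only remaining safeguard.

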### Participants and recruitment

Participants with unilateral CS will be recruited from attendance at a specialist neurosurgery clinic in a large tertiary hospital located in Townsville, Australia. The study specialists, comprising consultant neurosurgeons, will perform a medical evaluation to gain relevant medical and medication history and screen the patient against the eligibility criteria. This initial intervention will include baseline scores for VAS, ODI and HLOC. The patient will then be directed to the trial pharmacist, who will remain independent of the treating team, for consent and signature of the informed consent document.

Patients are deemed eligible if they meet all of the following criteria:Pain radiating into one leg only to, at or below knee levelMagnetic resonance imaging/computed tomography-confirmed sciatica caused by a degenerative condition (e.g., degenerative disc disease, bone spur growth, degenerative scoliosis)Naive to PGB and GBP useAged 18 years or olderSufficient understanding of the English language or interpretation assistance available to complete the study treatment and assessments

Concomitant medication, including analgesics and central nervous system CNS depressants (paracetamol, NSAIDs, and opioids), can be continued as long as the medication dose has been stable for 30 days prior to the start of the study.

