Patients will be excluded if they meet any of the following criteria:Pregnant or breastfeeding women or females planning conception during the study periodPatient history or laboratory results that suggest the presence of inherited neuropathy or neuropathy attributable to other causes (hypothyroidism, vitamin B_12_ deficiency, connective tissue disease, amyloidosis, toxic exposure)Major organ system disease, diabetic cardiovascular autonomic neuropathy with abnormality in sympathovagal balance, baseline postural hypotension of more than 20 mmHgSpecific contraindications to PGB or GBP (allergy to or significant renal impairment); PGB and GBP are both predominantly renally excreted, so patients with an estimated creatinine clearance < 60 ml/minute will be excludedOther neurologic medications such as serotonin reuptake inhibitors (paroxetine, fluoxetine), dual (serotonin and noradrenaline) reuptake inhibitors (venlafaxine), benzodiazepines, anti-convulsant medications (valproic acid, carbamazepine), anti-psychotic medications (clozapine, olanzapine, risperidone) or bipolar disorder medications (lithium)People with a diagnosis of cancer, dementia, severe mental illness or other condition which will significantly reduce the ability to consent and/or fully undertake the programDiabetic and/or HIV-related neuropathies

If a patient is eligible, the unblinded independent trial pharmacist will gain informed consent and notify the research team. The participant will then be randomised, and the pharmacist will dispense and counsel on the study medications and arrange visit appointments with reminders. At this point, baseline data will be confirmed by the pharmacist as collected at the first visit, or subsequently via telephone, before the participant commences the study medication. Following baseline data collection, the researcher will instruct the participant to break the seal on the medication pack and commence the study medicine as per the dosage instructions. At this point, the participant is considered to have been included in the study.

To ensure consistency, the study researchers will ensure that the protocol is being followed and that good clinical practice is being monitored. General practitioners will be able to refer community patients into the trial via a trial specialist hotline contact number whereby the patient is screened by a study specialist to ensure consistency of enrolment.

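### The protocol claims a blinded outcome assessor but also places outcome collection at visits with the un-blinded trial pharmacist, and the two statements need reconciling

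*Protocol article*

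**What the plan says.** Under Randomisation and blinding the protocol article sets out the pharmacist's part: "The trial pharmacist (un-blinded) will generate a randomisation code using a computer-derived permuted block with varying block size sequence". The same person helps make up the kits: "The unblinded pharmacist will be involved in the preparation of the medication kits as per the randomisation schedule". The list is kept from everyone else: "The randomisation schedule will remain concealed from other researchers". The section closes with the claim at issue: "The randomisation process will ensure concealed allocation and blinding of the specialist, the participant and the outcome assessor".

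Under Participants and recruitment, study neurosurgeons screen for eligibility and take the first VAS, ODI and HLOC scores. Then: "The patient will then be directed to the trial pharmacist, who will remain independent of the treating team, for consent". Further on in that section, "the unblinded independent trial pharmacist will gain informed consent and notify the research team". Randomisation follows, and the pharmacist dispenses and confirms the baseline data.

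Data collection makes two statements about who gathers outcomes. It opens with "Data collection will be conducted by the study researchers via telephone, email or online at baseline", and continues with weeks 4, 8, 10, 14 and 18. It then describes the pharmacist consultations, which cover starting treatment, monitoring progress and adjusting dose, and says of them: "These visits will also incorporate a medical evaluation and collection of primary and secondary outcomes".

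**The concern.** Blinding of the assessor is a statement about the person who elicits and writes down the outcome. If that person made the randomisation list and packed from it, the outcome is not assessed blind, however well the capsules match.

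The measures are subjective. VAS and ODI are patient-reported but may be taken by telephone or face to face, where the collector's prompting can matter. Side effects, the key secondary outcome, are more exposed: they are sought by questioning and graded mild, moderate or severe, so the recorder's judgement enters the data directly.

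The cross-over design gives no protection here. A tendency to record one drug more favourably than the other acts in opposite directions on the two periods' drugs and ends up in each participant's paired difference, which is the quantity being tested. No later analysis can remove it.

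A second, smaller question concerns allocation concealment. The person who takes consent, the last step before randomisation, generated the sequence. Varying the block size protects against guessing by others, not against knowledge of the list.

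**Working it through.** The main check is a comparison of stated roles.

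| Task | Who, per the protocol article | Section |
|---|---|---|
| Generates the code | Trial pharmacist, un-blinded | Randomisation and blinding |
| Helps prepare kits from the schedule | Same pharmacist | Randomisation and blinding |
| Kept from the schedule | The other researchers | Randomisation and blinding |
| Screens eligibility, first scores | Study neurosurgeons (the specialist is stated to be blinded) | Participants and recruitment; Randomisation and blinding |
| Takes consent | Trial pharmacist | Participants and recruitment |
| Confirms baseline data | Trial pharmacist | Participants and recruitment |
| Collects data at baseline and weeks 4 to 18 | Study researchers | Data collection, first sentence |
| Visits at which primary and secondary outcomes are collected | Consultations with the trial pharmacist | Data collection, later in the same paragraph |
| Outcome assessor | Claimed blinded, not identified | Randomisation and blinding |

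The two Data collection rows cannot both be read with the last row unless someone other than the pharmacist takes the outcomes at the pharmacist's visits. The article does not say so. Nor does it say that the study researchers are blinded, or that the pharmacist is not one of them; concealment from *other* researchers suggests that the pharmacist is counted among them. That the pharmacist keeps the list is an inference from having generated it and from that same wording.

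The protocol gives no figure for assessor bias, so the size can only be illustrated.

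- Inputs from Sample size: SD 1.2, 30 evaluable patients, target difference 0.9, power 80%, type I error 0.05.
- Assumption 1: 1.2 is the within-patient SD per measurement. The article does not label it. Then SE = 1.2 × √2 / √30 = 0.310.
- Check of that reading against the plan: 0.9 / 0.310 = 2.90. With a t test on 28 degrees of freedom this gives power of 80%, which matches the stated 80% at 30 patients.
- Assumption 2: a constant drug-related recording shift b in VAS, with no true difference. Rejection probability = Φ(−1.96 + b/SE) + Φ(−1.96 − b/SE).

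| b (VAS points) | b/SE | Rejection under a true null |
|---|---|---|
| 0.1 | 0.32 | 0.051 + 0.011 = about 6% |
| 0.2 | 0.65 | 0.094 + 0.005 = about 10% |
| 0.3 | 0.97 | 0.161 + 0.002 = about 16% |

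If 1.2 were instead the SD of the paired differences, SE = 1.2 / √30 = 0.219, and the same shifts would give about 7%, 15% and 28%. None of the values of b comes from the documents.

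**The case against.** The strongest reply is that the article does assign data collection to the study researchers, at exactly the time points set for the outcomes. The sentence about the visits is passive and names no collector. It also mentions a medical evaluation, which at the initial visit is the neurosurgeons' task, so something done at a pharmacist visit need not be done by the pharmacist. The recruitment section separates the pharmacist from the research team. This stands: a reader might infer that the pharmacist definitely takes the primary outcomes and that blinded assessment has failed, but the text does not establish that. It establishes a contradiction.

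Participants rate their own leg pain and are blinded, and collection by email or online is allowed. This also stands. It narrows the risk for VAS and ODI to interviewer influence and leaves side-effect severity as the main exposure. The article does not say what share of contacts is by conversation.

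On concealment, one might infer that foreknowledge of the list undermines the randomisation. That goes too far. Specialists stated to be blinded screen eligibility before the pharmacist meets the patient, and every participant is due both drugs, so foreknowledge bears only on the sequence and on who enters it.

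A last reply is that delegation of duties belongs in the full protocol. That would excuse silence. It does not excuse two statements in the article that conflict on a claim the Discussion relies on for minimising bias.

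**Conclusion.** The inconsistency is real. The article claims a blinded outcome assessor, places outcome collection at consultations with the un-blinded pharmacist who generated the code, and in the same section gives collection to the study researchers. Followed as written, an un-blinded person may elicit or record VAS, ODI and especially side-effect severity. This conclusion rests on the stated roles alone and needs no numerical assumption.

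The size of any bias is unknown. The range of about 6% to 16% rejection under a true null, for shifts of 0.1 to 0.3 points, depends on assumed shifts and on an SD that the article does not label. It shows that a shift well below the 0.9-point target would matter; it is not an estimate of what will happen.

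The consent point is secondary: the concealment claim does not hold for the person taking consent, with limited consequence in this design.

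**What to change.** State in Data collection that VAS, ODI, HLOC and side-effect severity, at each scheduled assessment of these measures from baseline to week 18, are collected only by study researchers who are blinded and have no access to the schedule, or by direct participant self-completion by email or online. Delete outcome collection from the description of the pharmacist visits, and say explicitly that the pharmacist is not an outcome assessor. The other content of those visits is outside this point.

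Trial status reports 18 participants completed. Rewording cannot change how their outcomes were taken, so report for them who collected each outcome and whether that person was blinded.

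For consent, either have it taken by a blinded researcher outside the treating team, which keeps the independence the recruitment section asks for, or qualify the concealment claim so that it excludes the pharmacist.

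Cost: slightly more coordination between researcher contacts and pharmacist visits, and a formal amendment with ethics committee approval, as Modification of the protocol requires. The tasks move among existing staff.
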